**Fig. 2 Fig2:**
[figure not shown]
**a** The Walkbot-S™, an exoskeletal-type gait training robot; **b** a patient participating in gait training using Walkbot-S™

**Table 1 Tab1:** Walkbot-S™ reference and maximal velocities depending on height

	Height						
	140 cm	150 cm	160 cm	170 cm	180 cm	190 cm	200 cm
Reference velocity (m/s)	1.0	1.1	1.2	1.3	1.4	1.5	1.6
Maximal velocity (m/s)	1.8	2.0	2.2	2.4	2.6	2.8	3.0

**Table 2 Tab2:** Example of a training velocity protocol for a 160-cm tall participant

	No. of minutes						
	0–5	5–10	10–15	15–20	20–25	25–30	30
Training session no.	Velocity, m/s						
1	1.2	1.2	1.4	1.4	1.7	1.7	1.7
2	1.2	1.2	1.4	1.4	1.7	1.7	1.7
3	1.4	1.4	1.8	1.8	2.2	2.2	2.2
4	1.4	1.4	1.8	1.8	2.2	2.2	2.2
5	1.7	1.7	2	2	2.2	2.2	2.2
6	1.7	1.7	2	2	2.2	2.2	2.2
7	1.9	1.9	2.2	2.2	2.2	2.2	2.2
8	1.9	1.9	2.2	2.2	2.2	2.2	2.2
9	1.9	1.9	2.2	2.2	2.2	2.2	2.2
10	1.9	1.9	2.2	2.2	2.2	2.2	2.2
11	1.9	1.9	2.2	2.2	2.2	2.2	2.2
12	1.9	1.9	2.2	2.2	2.2	2.2	2.2

During gait training, the robot provides an auditory cue at the toe-off phase to improve gait rhythmicity. Moreover, the robot provides a visual feedback by displaying a warning message on the screen when the torque exceeds a preset target range, which induces active hip flexion. The cue and feedback are designed to induce active participation in the training. The treatment time per session is 45 min, including don-and-doff, warm-up, and cool-down. The actual RAGT time is 30 min. A total of 12 sessions are provided over the course of 4 weeks.

Participants in the treadmill training group receive gait training on the treadmill. The same velocity protocol as in the RAGT group is applied to the treadmill training group to match the training intensity. A physical therapist provides appropriate visual and auditory instructions to allow the patient to participate in gait training actively. The treatment time per session is 45 min, including warm-up and cool-down. The actual treadmill training time is 30 min. A total of 12 sessions are provided over the course of 4 weeks.

The participants are contacted by phone and mobile text message 1 day before each session to improve adherence. During the clinical trial, participants are prohibited from changing the regimen of dopaminergic medication but they are permitted to keep the previous rehabilitation therapy that was already received. The participation can be discontinued due to the occurrence of serious adverse events or at the participant’s request. Fidelity of the intervention will be assessed through documenting the number and duration of sessions and the minimal and maximal velocity of each session delivered.

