**Methods:**

This is a prospective, single-blind, single-center, randomized controlled trial. Eligible participants will be randomly allocated to: 1) a Walkbot-S™ RAGT group or 2) a treadmill training group. The participants will receive three 45-min sessions of each intervention per week for 4 weeks. Gait speed during RAGT will be targeted to the maximal speed depending on the participant’s height; the same principle will be applied to the treadmill training group to match the training intensity. The primary outcome measure is gait speed measured by the 10-Meter Walk Test at a comfortable pace under single-task conditions. Secondary outcomes include dual-task interference, the Berg Balance Scale, Timed Up and Go test, the Korean version of the Falls Efficacy Scale-International, New Freezing of Gait Questionnaire, Movement Disorder Society-sponsored revision of the Unified Parkinson’s Disease Rating Scale, and functional connectivity measured by resting-state functional magnetic resonance imaging. Baseline assessments (T0) will be conducted to acquire clinical characteristics and outcome measure values before the intervention. Postintervention assessments (T1) will compare immediate efficacies within 3 days after the intervention. Follow-up assessments (T2) will be conducted 1 month after the intervention. Considering an alpha of 0.05 and a power of 80%, the total number of participants to be recruited is 44.

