## Background

Robot-assisted gait training (RAGT) was developed to restore gait function by promoting neuroplasticity through repetitive locomotor training [1]. Exoskeletal and end-effector robots have been commercialized and utilized in gait rehabilitation [2]. In the area of brain diseases, most clinical studies have been conducted on stroke patients. According to a recent systematic review, machine- and robot-assisted gait training improved walking independency in subacute stroke patients who could not walk by themselves [3]. The American Heart Association/American Stroke Association (AHA/ASA) guideline for adult stroke rehabilitation recommended RAGT to improve motor function and mobility with a class IIb level of evidence A [4]. However, there is still a lack of studies of RAGT in brain diseases other than stroke, and clear guidelines are not provided.

Parkinson’s disease (PD) is a neurodegenerative disorder presenting with resting tremor, rigidity, bradykinesia, postural instability, and gait disturbance. Gait disturbance is one of the most disabling symptoms of PD [5]. Reduced step height, short stride, slow gait, and freezing of gait are common gait problems in patients with PD. Although pharmacological treatment has been the mainstay of PD management, most patients experience functional aggravation despite optimal medication [6]. Deep brain stimulation, a surgical intervention to treat PD, has become an acceptable treatment option. However, because of the risks and complications of the procedure, it has been limited to some advanced patients with medically refractory symptoms [7]. So far, no cure for PD has been developed. Therefore, rehabilitation has been an essential element in maintaining the maximum level of mobility and independence in patients with PD. For gait rehabilitation in PD, treadmill training has been a common approach. Thus, conventional treadmill training was selected as a comparator in this study protocol.

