### Sample size

The primary outcome measure in this study is gait speed in postintervention assessments measured by the 10-m walk test (10MWT) at a comfortable pace under single-task conditions. Previous studies, in which similar populations and intervention protocols were employed, have reported that the minimal detectable change in comfortable gait speed measured by the 10MWT was 0.18 m/s [27] and the standard deviation was 0.08–0.20 m/s [13, 17]. Based on those findings, we consider 0.18 m/s as a clinically significant improvement in gait speed and 0.20 m/s as an acceptable standard deviation. Consequently, 20 participants per group will be required to achieve 80% power with a two-tailed α of 0.05, as determined by [28]:$$ N=\frac{2{SD}^2{\left({Z}_{\alpha }+{Z}_{\beta}\right)}^2}{\triangle^2} $$

With an expected drop-out rate of 10%, a total of 44 participants should be recruited, 22 for each group, to establish the relative efficacy of each intervention in improving gait velocity.

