### Interventions

Participants in the RAGT group will receive gait training with the Walkbot-S™ (P&S Mechanics, Seoul, Korea) for 12 sessions (Fig. 2). Training is preceded by fitting and adapting the equipment to the participant. In the first training session, RAGT starts at the reference velocity depending on the participant’s height (Table 1) and reaches 80% of the maximal velocity at the end. Starting with the third training session, the initial gait velocity is increased and the final velocity becomes the maximal velocity depending on the participant’s height. Starting with the seventh training session, training velocity reaches the maximal velocity after 10 min. Table 2 shows an example of a training protocol for a participant whose height is 160 cm.

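### Tables 1 and 2 set training speeds in m/s that Hoehn-Yahr 2.5–3 patients are very unlikely to sustain on a treadmill, so the unit or the values need checking and correcting

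*Protocol article*

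**What the plan says.** Table 1 (Methods, Interventions) lists two speeds for each height from 140 to 200 cm. Its row labels begin "Reference velocity (m/s" (values 1.0 to 1.6) and "Maximal velocity (m/s" (values 1.8 to 3.0). Table 2 works the schedule through for a height of 160 cm, and its header also gives m/s.

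These are scheduled targets, not only device limits. The abstract says "Gait speed during RAGT will be targeted to the maximal speed", with height as the only determinant. The Interventions text has session 1 end at 80% of the maximum and has sessions from the third onward end at the maximum. From the seventh session, "training velocity reaches the maximal velocity after 10 min".

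The treadmill arm follows the same schedule. The abstract states that "the same principle will be applied to the treadmill training group to match the training intensity", and the Interventions section repeats it: "The same velocity protocol as in the RAGT group is applied to the treadmill training group to match the training intensity".

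Participants are at Hoehn-Yahr stage 2.5 or 3 (Participants). On gait in this disease, the Background says "Reduced step height, short stride, slow gait, and freezing of gait are common gait problems in patients with PD". It goes on to describe lower cadence and longer double support.

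**The concern.** Read as printed, the schedule asks people with moderate Parkinson's disease to train for long stretches at what most readers would call a jog. In the control arm they would do so without an exoskeleton. That sits badly with the article's own account of slow, short-stepped gait.

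The two tables are the published definition of dose in both arms. If the unit or the numbers are misprinted, the arms are still nominally matched, but the printed dose is wrong. A site copying it could then run a treadmill much too fast for patients prone to freezing: 3.6 times too fast if km/h was meant. If the unit is right, it is doubtful whether treadmill participants can reach the target, and with it whether intensity is matched.

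**Working it through.** **Inputs.** All speeds come from Tables 1 and 2. Training time is 30 minutes per session for 12 sessions (Interventions), which is 360 minutes or 21,600 s. I treat the last column of Table 2 (minute 30) as an end point with no duration.

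**Do the tables agree with each other and with the text?** At 160 cm Table 1 gives a reference of 1.2 and a maximum of 2.2. Table 2 starts at 1.2 and peaks at 2.2. The 80% rule gives 0.8 × 2.2 = 1.76, printed as 1.7. The step changes at sessions 3 and 7 match the text. The m/s label is therefore used consistently in three places and is not a slip in one cell.

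**Conversion (km/h = m/s × 3.6).**
- Maximal speeds: 1.8 × 3.6 = 6.5 km/h at 140 cm; 2.2 × 3.6 = 7.9 at 160 cm; 3.0 × 3.6 = 10.8 at 200 cm.
- Reference speeds: 1.0 × 3.6 = 3.6 km/h at 140 cm; 1.6 × 3.6 = 5.8 at 200 cm.

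**Time at the maximum, 160-cm example.** Sessions 3–6: 4 × 10 = 40 min. Sessions 7–12: 6 × 20 = 120 min. Together 160 of 360 min = 44%.

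**Distance, 160-cm example.** Each session has three 10-minute speed levels, so distance = 600 s × their sum.

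| Sessions | Speeds (m/s) | Distance per session |
|---|---|---|
| 1–2 | 1.2, 1.4, 1.7 | 600 × 4.3 = 2,580 m |
| 3–4 | 1.4, 1.8, 2.2 | 600 × 5.4 = 3,240 m |
| 5–6 | 1.7, 2.0, 2.2 | 600 × 5.9 = 3,540 m |
| 7–12 | 1.9, 2.2, 2.2 | 600 × 6.3 = 3,780 m |

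Total: 2 × (2,580 + 3,240 + 3,540) + 6 × 3,780 = 41,400 m. Mean speed: 41,400 / 21,600 = 1.92 m/s = 6.9 km/h. From session 7 the mean is 3,780 / 1,800 = 2.1 m/s = 7.6 km/h.

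**What that asks of the patient.** The article gives no step length, so I assume a range of 0.5 to 0.8 m. Steps per minute = speed × 60 / step length:
- at 0.8 m: 2.2 × 60 / 0.8 = 165;
- at 0.5 m: 2.2 × 60 / 0.5 = 264.

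From session 7 this would be held for 20 consecutive minutes by patients from a population whose stride and cadence the Background describes as reduced.

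**If the printed numbers were km/h (unconfirmed; divide by 3.6).** Maximal speeds become 0.50 to 0.83 m/s, reference speeds 0.28 to 0.44 m/s, and the 160-cm total 41.4 / 3.6 = 11.5 km.

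**The case against.** The strongest reply is that the article contains no figure against which these speeds can be called unachievable. It gives no baseline or tolerated speed, and the Background describes gait in Parkinson's disease in general and in words only. The tables agree with each other and with the text. Table 1 describes the device, and the device settings are not available here. All of this stands. The conclusion is a judgement resting on a stated assumption, not a contradiction proved from the text.

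Safeguards can also be cited: ethics and regulatory approval, exclusion of severe medical problems and of other disorders affecting the legs, and discontinuation for serious adverse events or on request. They are real, but none of them settles the unit. A rule for lowering speed may well be in the full protocol, and its absence from a condensed article is no fault. What is questioned here is the numbers the article does print.

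A reader might infer more than the article supports:
- *That km/h was simply mistyped.* That reading gives reference speeds of only 0.28 to 0.44 m/s, and nothing confirms it. The values need checking as well as the unit.
- *That participants are asked to run at 10.8 km/h.* That figure applies only at 200 cm. The one worked schedule peaks at 7.9 km/h.
- *That the rise from reference to maximal speed is implausible because it is several times the 0.18 m/s in the Sample size section.* That figure refers to something else: "the minimal detectable change in comfortable gait speed measured by the 10MWT was 0.18 m/s". A scheduled rise in training speed is a different quantity, so the ratio is not evidence.
- *That the arms are not matched.* This would follow only if m/s is meant and treadmill participants fall short of it. The article shows neither.

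**Conclusion.** The point holds as a query that calls for correction. As printed, the 160-cm schedule puts 160 of 360 minutes (44%) at 7.9 km/h and covers 41.4 km, in both arms. On the assumption that patients at Hoehn-Yahr 2.5–3 with slow, short-stepped gait cannot sustain jogging speed on a treadmill without an exoskeleton, the unit or the values are very likely wrong. The article does not show which.

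The consequence is for the definition of the dose, its safe replication and, only if m/s is intended, the claim of matched intensity. The sample size, the endpoint and the primary test are unaffected. It should be fixed; my confidence is moderate because no achievable speed is given.

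**What to change.** Check the unit and the values in Tables 1 and 2 against the device settings and against the lowest and highest speeds that the fidelity log already records for each session, then correct both tables. The Trial status section says recruitment has begun and is continuing, so logged sessions should be available. The cost is a look-up and a correction to two tables. If they were misprinted, nothing more is needed.

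Only if m/s is truly intended: cap treadmill speed at what each participant tolerates, summarise delivered speeds by arm from the same log, and limit the statement about matched intensity to what was delivered. The downside is a weaker matching claim, because the arms may then openly differ in training speed.

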### Outcome measures

The primary outcome measure is gait speed measured by the 10MWT at a comfortable pace under single-task conditions [29]. The 10MWT is a common measure to evaluate gait velocity and highly reliable for assessing gait speed in patients with PD [29].

The secondary outcomes include dual-task interference [30], the Berg Balance Scale (BBS) [31], Timed Up and Go (TUG) test [32], the Korean version of the Falls Efficacy Scale-International (KFES-I) [33, 34], the New Freezing of Gait Questionnaire (NFOG-Q) [35], and the Movement Disorder Society-sponsored revision of the Unified Parkinson’s Disease Rating Scale (MDS-UPDRS) [36].

Dual-task interference, an indicator of gait automaticity, is defined by the difference between dual- and single-task performance [37]. To evaluate dual-task performance, cognitive dual-task walking [38] will be measured while performing the Wechsler Forward Digit Span [39], and physical dual-task walking will be measured while carrying a tray with two cups of water [40, 41]. The BBS measures balance function during sitting, standing, and changing positions. It consists of 14 items and the total score ranges from 0 to 56 [42]. The tool is clinically valid in PD patients [31]. The TUG test is a reliable measure for mobility in the elderly. During the test, patients stand up from a chair, walk for 3 m, turn, walk back, and sit down. It is also a highly reliable tool to assess mobility in PD [32]. KFES-I is a valid method to assess fear of falling in the elderly [33]. It is a self-reported measure of concerns about falls during activities of daily living. It consists of 16 items scored on a four-point scale [34]. NFOG-Q is a freezing of gait (FOG) questionnaire which assesses FOG severity and gait disturbances. It is a reliable tool to measure the FOG and the functional impact in patients with PD [35]. MDS-UPDRS, a clinical rating scale for PD, contains four parts [36]. A total of 50 questions rate disability or impairment on a scale of 0–4.

The 10MWT, BBS, and TUG test will be assessed by a physical therapist and the MDS-UPDRS will be administered by a licensed clinician. All assessors will be blinded to group assignment. Figure 3 shows the schedule for outcome measures evaluated at each visit.

**Fig. 3 Fig3:**
[figure not shown]
Study schedule of enrollment, interventions, and assessments. 10MWT 10-m walk test, BBS Berg Balance Scale, KFES-I Korean version of the Falls Efficacy Scale-International, MDS-UPDRS Movement Disorder Society-sponsored revision of the Unified Parkinson’s Disease Rating Scale, NFOG-Q New Freezing of Gait Questionnaire, RAGT robot-assisted gait training, rs-fMRI resting-state functional magnetic resonance imaging, TUG Timed Up and Go

### Functional MRI

Functional MRI will be employed to analyze functional connectivity before and after the intervention. Images will be obtained by a 3-T scanner (Siemens Magnetom TrioTim) using the following parameters: 116 volumes with a matrix size of 128 × 128 mm and a voxel size of 1.88 × 1.88 × 4.20 mm, TR = 3500 ms, TE = 30 ms, flip angle = 90°, and FOV = 240 × 240 mm. All participants will be instructed to remain still but awake with the eyes closed during the resting-state functional MRI scan.

### Data collection, management, and dissemination

Demographic data including age, sex, height, duration of disease, Hoehn-Yahr stage, MMSE score, and comorbidities will be obtained. Outcome measures at T0, T1, and T2 will be acquired as well. All data will be de-identified using an identification number to provide confidentiality and will be collected on paper case report forms and password-protected digital files. Paper case report forms and digital files will be stored in a locked cabinet in a locked office and on a password-protected computer in a locked office, respectively. An independent clinical research assistant will verify the data by review of medical records once a month to guarantee data quality including completeness and accuracy. Any adverse events, any untoward medical occurrence associated with the intervention of this study, will be recorded and reported to the Institutional Review Board and Korean Ministry of Food and Drug Safety (KMFDS). Additional medical procedures will be provided depending on the event. Trial management may be audited by the KMFDS which is independent of investigators at any time.

All authors will have access to the final dataset. Upon completion, trial results will be reported to the funders and submitted to peer-reviewed journals to communicate to participants, healthcare professionals, and the public. Authorship will follow guidelines recommended by the International Committee of Medical Journal Editors (ICMJE). Professional writers will not be employed.

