**Discussion:**

This study will reveal the effect of RAGT using an exoskeletal robot, not only on gait speed, but also on gait automaticity, balance function, fall risk, quality of life, and disease severity. In addition, the study will shed new light on the mechanism of the RAGT effect by evaluating changes in gait automaticity and brain functional networks.

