### Randomization and blinding

Randomization and allocation will be performed using computer-generated block randomization with a block size of 4 and 6. An independent researcher who is not in contact with any patient will perform the randomized allocation. The ratio between the RAGT and treadmill training groups will be 1:1. Details of the allocated group will be given in sequentially numbered, opaque, sealed envelopes to the research assistants in sequential order. The principal investigator, outcome assessors, and data analysts will be blinded to the group allocations of the participants until statistical analysis.

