## Discussion

Robots have been increasingly used for gait rehabilitation, especially in patients with brain diseases such as stroke and multiple sclerosis [43, 44]. However, contradictory results have been reported by studies of RAGT in patients with PD. In addition, there are no clinical guidelines for RAGT in gait training for PD. Moreover, even in studies reporting gait improvement by RAGT in PD, the mechanism of the treatment effect remains elusive.

RAGT in this study will include a visual feedback and an auditory cue, which are known as effective strategies to treat locomotor impairments [45]. Feedback or cues were reported to improve gait performance in patients with PD [46], and an additional beneficial effect of cues with gait training has been suggested [47]. External cues appear to help patients with PD walk better by compensating for the impaired central drive for walking [48]. Another hypothesis is that external cues enable patients to utilize the intact premotor cortex, rather than the impaired basal ganglia/supplementary motor area circuit [49]. Therefore, RAGT including external cues or feedback is expected to improve gait performance in patients with PD.

This study will reveal the effect of RAGT using an exoskeletal robot, not only on comfortable gait speed, but also on dual-task interference, balance function, fall risk, and disease severity. In addition, the findings of the study will provide knowledge on the recovery of gait automaticity and brain functional connectivity following RAGT. We hope that the information acquired from this trial will advance our understanding of the mechanism of the RAGT treatment effect and improve clinical decision making when physiatrists consider gait training for patients with PD.

A limitation of this study is that it involves only one center. This might influence the generalizability of the results to other centers. Another limitation is that blinding of patients and therapists is not possible due to the definite different feature of the interventions.

In summary, this trial will compare the effects of RAGT with those of treadmill training on gait performance in patients with PD. The results of this study will provide clear evidence whether RAGT rather than treadmill training may be recommended for gait training in patients with PD.

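### The adverse event definition puts an unassigned relatedness judgement before recording, so harms, including falls outside sessions, may be under-counted, possibly unequally by arm

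*Protocol article*

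**What the plan says.** The protocol article covers recording of harms in one sentence under Data collection, management, and dissemination: "Any adverse events, any untoward medical occurrence associated with the intervention of this study, will be recorded and reported". The recipients are the review board and the national regulator. The sentence does not say who judges the association, whether it means cause or only timing, or over what period events are collected.

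Other statements bear on the point:

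- **Who knows the arm.** The Discussion accepts that "blinding of patients and therapists is not possible due to the definite different feature of the interventions". Randomization and blinding states: "The principal investigator, outcome assessors, and data analysts will be blinded to the group allocations of the participants until statistical analysis".
- **Data checking.** "An independent clinical research assistant will verify the data by review of medical records once a month", with completeness among its aims.
- **Falls.** The Background names fall risk among the secondary aims, and the Abstract promises effects not only on gait speed "but also on gait automaticity, balance function, fall risk, quality of life, and disease severity". The only listed measure that concerns falls directly is the KFES-I, of which Outcome measures says: "It is a self-reported measure of concerns about falls during activities of daily living".
- **Other use of adverse events.** Under Interventions: "The participation can be discontinued due to the occurrence of serious adverse events or at the participant’s request".

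**The concern.** A harms record is easiest to interpret when everything untoward is written down first and its cause is considered afterwards. Here the order appears reversed: the link to the intervention is part of what makes an occurrence an adverse event. An occurrence thought unrelated falls outside the definition, and nothing else in the article requires it to be kept.

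Two features of this trial make that matter. First, early reports will probably come from people who know the arm: patients for events between sessions, therapists for events within them. An exoskeleton and an ordinary treadmill may invite different opinions about cause. Even a blinded judge would see only what these people pass on.

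Second, falls are part of the trial's own question. Participants are at Hoehn-Yahr stage 2.5 or 3, and the Background links impaired gait automaticity to falls. Yet no listed outcome is described as a count of falls: the KFES-I addresses worry about falling, and the Berg Balance Scale and Timed Up and Go address balance and mobility. Adverse event recording is thus the only route described by which actual falls could be captured, and a fall at home is the kind of event most readily judged unrelated to training. The Discussion expects the trial to inform whether robot training should be recommended over treadmill training, and comparable harm data would serve that aim.

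**Working it through.** **1. What the wording does to three falls**

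The key word can be read as causal or as temporal.

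| Event | Causal reading | Temporal reading |
|---|---|---|
| Fall during a session | Recorded if attributed to training | Recorded |
| Fall at home within the 4 training weeks | Recorded only if attributed to training | Probably recorded |
| Fall at home between T1 and T2 | Recorded only if attributed to training | Unclear, since training has ended |

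On the causal reading, all three depend on a judgement. On the temporal reading, the third remains open. Neither reading clearly secures every fall up to T2.

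**2. Whether another provision closes the gap**

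- *Blinding.* The principal investigator, assessors and analysts are blinded, but the judgement of association is not assigned to any of them.
- *Monthly record review.* It can find events that reached the medical record. It does not widen the definition, and a fall without medical contact would leave no trace there.
- *Outcomes.* None of those listed is described as counting falls.

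**3. Size, on assumed values**

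The article states no adverse event or fall rate, so it offers no figure on this point to reproduce. The only input taken from it is 22 per arm (Sample size: 20 per group plus 10% = 22; 2 × 22 = 44). All risks and attribution rates below are assumptions.

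Let *p* be the true event risk, equal in both arms, and let *a* and *b* be the shares of events judged associated in the two arms.

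- Expected recorded counts: 22 × *p* × *a* and 22 × *p* × *b*
- Ratio of recorded counts: *a* / *b*, whatever *p* is
- Share of all events lost: 1 − (*a* + *b*)/2

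| *p* | True events per arm | 80% and 80% | 80% and 40% | 50% and 30% |
|---|---|---|---|---|
| 10% | 2.2 | 1.8 v 1.8 | 1.8 v 0.9 | 1.1 v 0.7 |
| 20% | 4.4 | 3.5 v 3.5 | 3.5 v 1.8 | 2.2 v 1.3 |
| 30% | 6.6 | 5.3 v 5.3 | 5.3 v 2.6 | 3.3 v 2.0 |
| 50% | 11.0 | 8.8 v 8.8 | 8.8 v 4.4 | 5.5 v 3.3 |
| Share lost | | 20% | 40% | 60% |

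The same in whole numbers, with 5 true falls per arm:

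- 80% and 40%: 5 × 0.8 = 4 against 5 × 0.4 = 2. This is an apparent doubling with no true difference, and 4 of 10 falls are lost.
- 80% in both arms: 4 against 4, with 2 of 10 lost.
- 40% and 80%: 2 against 4, so the distortion can run either way.

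Two effects must be kept apart. Under-counting follows whenever some events are judged unassociated. Imbalance arises only if that judgement differs by arm.

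**The case against.** The case on the other side is substantial.

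- **The sentence does not contain the word *only*.** Association may mean timing, and no causality assessment is mentioned. This stands as a caution: the causal reading is the plain one but not the only one. A rule that admits both still needs settling.
- **A reader might infer that unblinded staff decide what is recorded.** The article does not say so. It says therapists cannot be blinded, not that they classify events, and it blinds the principal investigator and assessors. What remains is that no judge is named and that the likely first reporters know the arm.
- **A reader might infer that the arms cannot be compared fairly on safety.** That goes too far. One definition covers both arms, and with equal attribution events are lost but balance is kept. Unequal attribution is neither stated nor excluded.
- **The record review and possible regulatory audit are safeguards.** This is right in part, since the review bears on completeness, but only for what reaches a record.
- **Fall counts would be an extra outcome, with little precision in 44 participants.** This is fair as to efficacy. The request here is to capture falls as harms, not to test them.
- **A journal article condenses a fuller protocol.** Collection windows, form fields and safety tables may well be there, and their absence here is no fault. The point rests on the definition that the article does state.

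**Conclusion.** The point holds in a limited form. The stated definition, read plainly, makes a judgement of relatedness a condition for recording and assigns it to no one. Harms judged unrelated, including falls outside sessions, may therefore be under-counted, possibly unequally by arm. The monthly record review reduces the risk but does not remove it, and no listed outcome supplies a fall count.

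The size cannot be estimated from the article. The illustrative loss of 20% to 60% of events, and the doubling of 4 against 2, come wholly from assumed attribution rates. They show how the rule could act, not what will happen. Differential bias is a risk and has not been shown.

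The primary gait speed analysis and the sample size are untouched. This is an inexpensive improvement to the safety data, best made before events occur, because events left unrecorded are hard to recover reliably later.

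**What to change.** Change the definition under Data collection, management, and dissemination so that:

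1. every untoward medical occurrence in both arms is recorded from randomization to T2, inside or outside sessions, whatever its suspected cause;
2. falls are asked about in the same words in both arms at existing contacts (the training sessions, T1 and T2);
3. relatedness is rated afterwards as a separate field, preferably by someone blinded to arm;
4. all events, and falls among them, are tabulated by arm, with the related subset shown alongside.

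If the full protocol already works this way, correcting the published sentence is enough.

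The cost is one extra question at contacts that already take place, a line on the case report form, and a larger number of recorded events to process. No additional participants or visits are needed.
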